#### 3.8.4. Sample Size Considerations

We assume one half of the intervention effect to be present in the period when the respective study site crosses to the intervention condition and the full intervention effect to be present for all subsequent periods. SDM with parents, the primary endpoint, is assessed in the cross-sectional component using the binary CollaboRATE^pediatric^ score that differentiates between suboptimal and optimal extents of perceived SDM [37]. Assuming a time constant cluster effect with standard deviation 0.06 of the cluster specific proportions of responses indicating an optimal extent of SDM, a practically relevant difference between 0.60 and 0.675 can be detected with a two-sided test with type 1 error of 0.05 and a power of 0.80, if 61 parents are sampled in each SPC in each quarter. Allowing for 10% incomplete questionnaires, we aim to sample 70 parents per study site and quarter. Sensitivity analyses relaxing simplifying assumptions (e.g., constant sample sizes across periods and study sites, no time varying cluster effects) did not affect the power calculations substantially. We expect that the proportion of parents providing data on more than one occasion will be very small, so this will be ignored for purposes of power calculation and in the analyses.

#### 3.8.5. Participants

##### Cross-Sectional Component

We invite all parents having an appointment at one of the SPCs to participate in this component of the evaluation without applying any further inclusion or exclusion criteria. Children are invited to participate starting at age seven years (grade 2 of primary school) when most children have acquired sufficient reading and writing competencies to complete a short questionnaire. However, parents and children lacking German language skills that would allow them to complete a short questionnaire or children with severe cognitive disabilities (assessed by parent reports) are excluded *de facto*.

##### Cohort Component

Parents are eligible for participation if (1) they are able to complete a questionnaire in German, (2) their child is aged 3–16 years and (3) they are expected to have at least four more appointments at the SPC over the following two years. Children of participating parents aged seven years and older with sufficient German language skills and without severe cognitive disabilities (based on parental assessment) are also invited to participate in this part of the evaluation. We exclude parents with children aged below 3 years because there is no conceptual clarity on involvement in life situations in this age group and valid instruments for assessing participation are not available [38].

#### 3.8.6. Recruitment and Data Collection

##### Cross-Sectional Component

Data are collected on one randomly selected day per week during the entire study duration. To prevent the pre-selection of participants in the evaluation, study sites are notified no more than eight days in advance about the next data collection day. The study statistician used a block randomization scheme such that three Mondays to Wednesdays and two Thursdays and Fridays were randomly selected per quarter. Upon registration, receptionists invite all parents and children seven years and older to participate. After the appointment, parents and older children are reminded about the questionnaires and are asked to complete them in the reception area. Completed questionnaires are deposited in a locked box at each study site. In general, participants complete the survey only once. While we cannot rule out that a small number of families take part multiple times, this is quite unlikely as most families have appointments at the SPC only every couple of weeks and data is collected on one random day per week. Given logistical constraints at several study sites including lack of internet access, it is not feasible to provide participants with an option to complete an online survey *in lieu* of a paper-and-pencil questionnaire. While completing an online survey is a convenient way of participation for a subset of parents, we do not anticipate that the mode of administration will induce selection bias.

##### Cohort Component

SPC staff recruit eligible parents and children consecutively at the end of their appointment. After informing the families about the study, staff obtain written informed consent from parents and children.

The closed cohort comprises three parent and child surveys completed once every six months. Depending on their preferences, families complete paper-and-pencil or online surveys implemented in Limesurvey (Version 2.65.0, LimeSurvey GmbH, Hamburg, Germany). Completed surveys are either returned by mail using prepaid reply envelopes or are submitted online. To minimise loss to follow-up, participants receive up to three reminders by mail or email.

#### 3.8.7. Endpoints

We use previously validated instruments to assess the primary and all secondary endpoints. All endpoints, their method of operationalisation and references to validation studies are summarised in Table 2. Secondary endpoints assessed in the cohort component are included in all three surveys.

#### 3.8.8. Statistical Analyses

To assess the intervention effect on perceived SDM with parents (primary endpoint; binary variable: optimal versus suboptimal perceived SDM) we will fit a marginal model for correlated binary data using generalised estimation equations and complete cases. The model will be applied to data aggregated at the level of study sites and study periods and will comprise fixed effects for study period and an intervention indicator. The intervention indicator will be set to 0, 0.5 and 1 for control, the first intervention and all subsequent intervention periods, respectively. For the sequence of eight random period effects per SPC, we specified a compound symmetry correlation structure with homogeneous variances. The Mancl and DeRouen method will be used to account for inflation of standard errors and type one errors [44]. The intervention effects will be reported as odds ratios with 95% confidence intervals contrasting the intervention condition to the control condition. The SAS Code for fitting the model for the primary endpoint is provided in Online Supplementary File S1. We will apply equivalent modeling strategies for the other binary endpoints in the cross-sectional component. For continuous endpoints in the cross-sectional component, we will fit linear mixed models with fixed effects for study period and intervention indicator and random effects at the SPC and SPC-period level using robust variance estimation.

For continuous endpoints in the cohort component, we will fit linear mixed models using survey wave as a discrete time variable. The models will comprise random intercepts at SPC, SPC-survey and subject levels, respectively, and fixed effects for survey wave, intervention indicator and age. The intervention indicator will be defined as above. When applicable, we will use robust standard errors and Wald tests based on sandwich estimators for effect estimation.

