## 3. Methods and Analysis

### 3.1. Study Design

The study design reflects the UK Medical Research Council guidance for the assessment of complex interventions [31] and comprises two parts. The effectiveness evaluation is based on a stepped wedge cluster randomised trial (Figure 2) with all study sites receiving the intervention at one of five randomly allocated time points. After a three-month pre-rollout period, three study sites cross from the control to the intervention condition every three months. Together with a three-month post-rollout period after the last study sites receive the intervention, the total length of the effectiveness evaluation is 21 months. The process evaluation uses a convergent mixed-methods design [32] to assess the implementation process of the PART-CHILD intervention, to uncover mechanisms potentially leading to intervention effects and to explore contextual factors that may moderate intervention effectiveness.

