### 3.4. Setting

The intervention is implemented in 15 Social Paediatric Centres (SPCs) across Germany. SPCs are secondary and tertiary healthcare facilities providing diagnostic, counseling and treatment services for children aged 0–18 years with special healthcare needs or suspected to have special healthcare needs. This includes, but is not limited to children with neurological, neurodevelopmental and behavioural chronic health conditions and disabilities (e.g., epilepsy, cerebral palsy or attention deficit hyperactivity disorder). The 156 German SPCs are interdisciplinary, physician-led outpatient clinics consisting of paediatricians (often with sub-specialty training in neuropaediatrics), psychologists, physiotherapists, occupational therapists, other allied health professionals like nurses or music therapists, and social workers.

SPCs vary considerably in terms of size and the range of services provided. For example; more than two-thirds of German SPCs provide specialised interdisciplinary diagnostic work-ups only (henceforth *diagnostic SPCs*) with recommended therapeutic services provided by other healthcare providers. The remaining SPCs provide both diagnostic work-ups and in-house therapeutic services (henceforth *diagnostic and treatment SPCs*).

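### Continuous secondary endpoints: the plan fixes sandwich-based inference on 15 sites without carrying over the small-sample correction it names for the binary endpoints

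*Protocol article*

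**What the plan says.** Section 3.8.8 of the protocol article treats two classes of endpoint differently.

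- **Binary endpoints.** The primary endpoint is analysed by a marginal model with generalised estimating equations. The Mancl and DeRouen method is named as protection against distorted standard errors and type 1 error. Other binary cross-sectional endpoints follow the same strategy.
- **Continuous cross-sectional endpoints.** These get linear mixed models with "random effects at the SPC and SPC-period level using robust variance estimation". No correction, test or reference distribution is named.
- **Continuous cohort endpoints.** These get linear mixed models with random intercepts for site, site-by-survey and subject. The inference sentence opens with the qualifier *when applicable* and continues: "we will use robust standard errors and Wald tests based on sandwich estimators for effect estimation". No correction or degrees of freedom are named.

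The number of independent units is the same in every model: "The intervention is implemented in 15 Social Paediatric Centres (SPCs) across Germany".

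**The concern.** A sandwich variance estimates the sampling variance from the squared residuals of the independent clusters. With 15 clusters this goes wrong in two ways. Fitted residuals are smaller than true errors, so the variance is biased downward. The variance estimate is also noisy, so a normal reference is too optimistic. The authors recognise the problem, since they name a remedy for it for the primary endpoint. That remedy is not carried over to the continuous models in the same section, although those models also rest on 15 sites.

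At stake are the intervals and p-values for the Table 2 secondary endpoints, to the extent that they are analysed as continuous: satisfaction with care (parent and patient), participation (CASP), quality of life (parent and patient report), utilisation and unmet needs, and parental stress. Participation matters most. The article treats shared decision-making as a possible antecedent of it, and it is measured only in the cohort, where the shortfall proves largest.

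**Working it through.** **1. Design, checked against the plan's own figure.** Section 3.1 gives 15 sites; "three study sites cross from the control to the intervention condition every three months"; and "the total length of the effectiveness evaluation is 21 months", so 21/3 = 7 periods. Section 3.8.8 gives the coding: "The intervention indicator will be set to 0, 0.5 and 1 for control, the first intervention and all subsequent intervention periods, respectively". The article states no type 1 error for the continuous endpoints. The figure that can be reproduced is the primary power (section 3.8.4: 0.60 v 0.675, site SD 0.06, 61 parents per site and quarter, power 0.80).

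The information on the effect from site-period means, after period effects, is

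[Σ(X − X̄_period)² − τ²/(σ² + Tτ²) · Σ_site(row sum − mean row sum)²] / σ²

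- σ² = 0.6375 × 0.3625 / 61 = 0.003788; τ² = 0.06² = 0.0036; T = 7
- First sum: 48.75 − 596.25/15 = 9.0. Second sum: 213.75 − 52.5²/15 = 30.0
- τ²/(σ² + 7τ²) = 0.0036/0.02899 = 0.1242
- Information = (9.0 − 0.1242 × 30)/0.003788 ≈ 1392, so SE = 0.0268
- 0.075/0.0268 = 2.80, and Φ(2.80 − 1.96) = 0.80

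The stated power is reproduced, so this reading of the design is sound. Section 3.8.8 also refers to "For the sequence of eight random period effects per SPC", which does not match seven periods. That is a separate point; the simulation below was run with 7 and with 8, with similar results.

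**2. Null simulation.** There were 20,000 runs per scenario (Monte Carlo SE about 0.002). The balanced site-period-mean form of the linear mixed model was fitted by REML. Assumed inputs:

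- *Cross-sectional:* ICC 0.015 to 0.10 (the lower end is 0.0036/0.24 = 0.015, from the primary endpoint), cluster autocorrelation 0.6 to 1.0, 61 per cell, plus one case with unequal variances.
- *Cohort:* three waves, three variance ratios and four wave timings (three at the stated six-month spacing, one wider).
- *Residual-type df:* cells − sites − (periods − 1) − 1. This is 105 − 15 − 6 − 1 = 83 for 7 periods, 120 − 15 − 7 − 1 = 97 for 8 periods, and 45 − 15 − 2 − 1 = 27 for the cohort.

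| Nominal 5% test | Cross-sectional | Cohort |
|---|---|---|
| Mean plain sandwich SE / true SD | 0.88–0.90 | 0.86–0.89 |
| Plain sandwich, normal reference | 9.5–10.5% | 10.1–11.8% |
| Plain sandwich, residual-type df | 9.0–10.1% | 8.9–10.3% |
| Plain sandwich, t(13) | 6.9–7.6% | 7.6–8.7% |
| Mancl-DeRouen, normal reference | 5.6–6.4% | 6.0–6.8% |
| Mancl-DeRouen, t(13) | 3.8–4.5% | 4.1–4.8% |
| Model-based SE, residual-type df | 5.1–5.6% | 5.0–5.7% |

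A second null simulation gave plain standard errors 8 to 11% too small, type 1 error of 9 to 11% (normal) and 6.5 to 8% (t(13)), and about 4% for Mancl-DeRouen with t(13).

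**3. Plausibility by hand.** If the standard error were exactly 0.86 to 0.90 of its true value and not random, the normal test would reject with probability 2Φ(−1.96 × 0.86) = 9.2% to 2Φ(−1.96 × 0.90) = 7.8%. The remaining excess is the noise in a variance estimated from 15 clusters.

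**The case against.** The strongest reply is that the article never says the sandwich is uncorrected. Mancl-DeRouen is itself a sandwich estimator, and a test built on it is a Wald test, so the wording is compatible with the remedy. A condensed article may also leave the sandwich variant and degrees of freedom to an analysis plan that is not shown. This stands in part: that no correction is used is an inference from the contrast within one section. But the article does not stay silent on the method. It states the variance estimator for both components and the test for the cohort, and it names the correction for one class of endpoint only. Followed as written, the continuous models get the plain sandwich.

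A reader might infer that every continuous endpoint is tested by an uncorrected Wald test and that type 1 error is simply doubled. The documents do not support that. The Wald sentence belongs to the cohort paragraph and is conditional; the cross-sectional sentence names no test. A doubling also needs a normal or residual-df reference, and none is stated. Nor can the inflation be compounded into a family-wise error rate as if the endpoints were independent. Several come from the same parents, two are versions of the same quality-of-life scale, and the article does not say that all are analysed as continuous.

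Two further limits stand. The simulation omits the cohort's age covariate and dropout, and its ICCs, autocorrelations and timings are assumptions. Section 1 (Objectives) describes the secondary endpoints as exploratory, which lowers the stakes but does not excuse intervals that are too narrow, since exploratory results are judged mainly by their intervals.

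**Conclusion.** The point holds in conditional form. If the plain sandwich is used as section 3.8.8 reads, standard errors for the continuous secondary endpoints are roughly 8 to 14% too small. Type 1 error is about 9 to 12% with a normal or residual-df reference and about 6.5 to 9% with t(13), so nominal 95% intervals cover about 88 to 91% or 91 to 93.5% respectively. None of the reference distributions examined brings the plain sandwich back to 5%. Model-based errors stay close to 5% when the working model is right, so most of the excess comes from the robust step. The size rests on the assumed ranges in the working, across which the direction did not change. The primary analysis carries its own named correction and is not affected.

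**What to change.** State one rule for every linear mixed model, cross-sectional and cohort. Either use a bias-corrected sandwich variance (for example Mancl-DeRouen, as for the binary endpoints) with a t reference based on the number of sites, or use model-based errors with Kenward-Roger degrees of freedom. Put that rule in place of the conditional *when applicable* sentence, so that the choice is fixed before the data are seen. If the unseen analysis plan already contains such a rule, the article's wording should be brought into line with it.

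No change to design or data collection is needed. The price is wider intervals: the t(13) quantile is 2.16 against 1.96, about 10% more from the reference alone, on top of the corrected standard error. Mancl-DeRouen with t(13) is slightly conservative (3.8 to 4.8% in the simulations). Kenward-Roger itself was not simulated; the nearest check is the model-based error with residual-type df, at 5.0 to 5.7%.

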### 3.9. Process Evaluation

Following existing guidance [36], we will (1) analyse intervention implementation using the RE-AIM framework [45], (2) explore mechanisms potentially explaining intervention effects and (3) investigate contextual factors that may act as barriers or facilitators to intervention implementation and effectiveness (Figure 5). We use a convergent mixed methods approach integrating qualitative and quantitative data [32]. Specifically, the database to which RE-AIM will be applied derives from baseline (A1 in Figure 5) and follow-up surveys (A2) and semi-structured telephone interviews with SPC directors and their staff (B) as well as comprehensive documentation of the intervention process based on implementation notes, *ICF-AddIn* usage and consultation observations.

#### 3.9.1. Participant Recruitment and Data Collection

##### Surveys among SPC Directors and Their Staff

We invite all eligible participants for team training to take part in two surveys administered at baseline prior to intervention implementation and at follow-up on a rolling basis approximately nine months after the team training (Figure 5). Following initial contact about study design and objectives, the SPC directors distribute written study information, the consent form and the paper-and-pencil baseline questionnaire to staff members, who are then asked to return completed documents in individually sealed envelopes to ensure confidentiality.

#### 3.9.2. Outcomes

##### Surveys among SPC Directors and Their Staff

As outlined in the description of our logic model, the baseline survey assesses preconditions for intervention implementation including (1) contextual factors (e.g., organisational readiness for change [validated scale: ORIC] [46], organisational culture [Competing Values Instrument] [47], perceived importance and feasibility of implementing patient- and parent-centred care [Patient involvement scale] [48]), (2) staff characteristics (e.g., professional backgrounds, level of awareness of the ICF-CY, perceived work satisfaction [Global Job Satisfaction Scale] [49]) and (3) patient characteristics (e.g., migration background, health insurance status).

The follow-up survey investigates changes in care practices and pathways to change using Likert scales and open-ended questions including (1) the implementation of training content and the use of the *ICF-AddIn* in daily routine care, (2) satisfaction with the intervention, (3) changes in perceived importance and feasibility of patient- and parent-centred care (Patient involvement scale) [48], (4) changes in perceived work satisfaction (Global Job Satisfaction Scale) [49] and (5) perceived barriers for the implementation of training content. Items for assessing some staff and patient characteristics were developed specifically for use in this study and have not been previously tested. The surveys are provided in Online Supplementary File S2.

##### Semi-Structured Interviews with SPC Directors and Their Staff

Telephone interviews explore staff perspectives on the implementation of the intervention in routine care and contextual barriers and facilitators. Specifically, the interview guide covers the relevance and use of intervention components, satisfaction and post-intervention changes in staff attitudes towards participation-centred care. Interviews with SPC directors cover additional meso-level contextual factors (e.g., time or financial resources). The interview guides are provided in Online Supplementary File S3.

#### 3.9.3. Analysis

##### Surveys among SPC Directors and Their Staff

We will assess changes in the perceived importance and feasibility of implementing patient- and parent-centred care and perceived work satisfaction between baseline and follow-up. Descriptive analysis will assess satisfaction with intervention content and the degree to which training content is implemented and the *ICF-AddIn* is used. In addition, associations between contextual factors at the level of staff (micro-level) and SPCs (meso-level) (independent variables) with process measures such as implementation, adoption and reach will be analysed.

##### Implementation Notes, ICF-AddIn Usage and Consultation Observations

A comprehensive documentation of the intervention implementation including notes, and quantification of the ICF-AddIn usage will allow operationalization of RE-AIM components such as Reach (e.g., percentage of staff participating in the team training), Implementation of each of the three intervention components (e.g., number of components selected from the implementation support program, usage of ICF-AddIn), Adoption and Maintenance (e.g., formation of ICF-working groups at the study sites). Compliance of SPC staff with motivational interviewing principles during child-parent-staff consultations are monitored in a subsample [51].

### 3.10. Integration of Quantitative and Qualitative Data

To examine implementation processes, pathways to impact and differences across subgroups of SPCs (e.g., high versus low performing SPCs based on percentage reached across all RE-AIM parameters) [52], qualitative and quantitative data will be integrated in several ways at the analysis and interpretation stage. At the analysis stage, we will partly transform qualitative into quantitative data (e.g., number of actions an SPC implements to support the transfer of training content into routine care). The transformed data will, in turn, be used in graphical displays integrating information from both data types. In addition, the transformed data will feed into exploratory analyses to gain insight into intervention processes and potential differential implementation and effectiveness across study sites. At the interpretation stage, results of the semi-structured interviews will provide rich contextual information contributing to the interpretation of quantitative findings.

